(H3) Since a perceived similarity of participants to expert patients might enhance the receptivity and self-efficacy of participants, it is hypothesized that participants who feel more similar to the expert patient they are assigned to have better outcomes in terms of ED symptomatology, self-efficacy, and experienced social support.(H4) It is hypothesized that, since the effectiveness of expert patients is theorized to come from effectively improving self-efficacy, changes in self-efficacy during the intervention period mediate subsequent long-term effects of the intervention on ED-related symptoms and experienced social support.

Thirdly, we aim to investigate practical experiences with Featback, such as intervention usage and user satisfaction.
(H5) It is expected that Featback with weekly expert-patient support will enhance intervention usage as well as satisfaction with the intervention compared to Featback alone.

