(H3) The third hypothesis concerned the relationship between the closeness or perceived similarity of participants with the expert patient they are assigned to, and ED symptomatology, self-efficacy, and experienced social support respectively. The effects of perceived similarity on the three dependent variables will be investigated for the short term (i.e., gains until post-intervention, T1) and the long term (i.e., gains until the last follow-up, T5), resulting in six linear regression analyses that need to be conducted. We correct for multiple testing for these analyses using Holm’s method.(H4) To investigate the fourth hypothesis that changes in self-efficacy during the 8-week intervention period mediate subsequent changes in ED-related symptoms and experienced social support (and not vice versa), a cross-lagged panel design will be used. For self-efficacy and the two outcome variables, change scores will be calculated for pre- (T0) to post-intervention (T1) and for post-intervention (T1) to long-term follow-up (T5; 12 months after T1). Next, hierarchical regressions will be performed, with post-intervention to long-term follow-up change of ED-related symptoms and experienced social support as dependent variables, and pre- to post-intervention change of self-efficacy as the independent variable. Additionally, the inverse relationships will be investigated. In other words, it will be examined whether changes in experienced social support or ED-related symptoms from pre- to post-intervention can predict post-intervention to long-term follow-up changes of self-efficacy. If the initial relationship is significant and the inverse relationship is not, a mediation effect of self-efficacy on ED-related symptoms and/or experienced social support is indicated. Corrections for autocorrelation and synchronous change will be applied to the mediation analysis.

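### H4 concerns mediation of the intervention's effect, but its decision rule tests only which change predicts which, so it can indicate mediation when support left self-efficacy unchanged

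*Protocol article*

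**What the plan says.** Under Aims and research questions, H4 is that "changes in self-efficacy during the intervention period mediate subsequent long-term effects of the intervention on ED-related symptoms and experienced social support". The reason given there is that expert patients are theorised to work by raising self-efficacy.

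Under Moderator and mediator analyses, H4 is restated as self-efficacy change mediating later changes in the two outcomes, and not the reverse. The intervention no longer appears in the statement. The test is a set of hierarchical regressions "with post-intervention to long-term follow-up change of ED-related symptoms and experienced social support as dependent variables". The only predictor that the text names for these models is the "pre- to post-intervention change of self-efficacy as the independent variable". The inverse models ask whether early change in either outcome "can predict post-intervention to long-term follow-up changes of self-efficacy".

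The inference rule is explicit: "If the initial relationship is significant and the inverse relationship is not, a mediation effect of self-efficacy on ED-related symptoms" and/or on social support is taken to be indicated. One adjustment is named: "Corrections for autocorrelation and synchronous change will be applied to the mediation analysis". The general two-tailed 0.05 level in Statistical analyses applies, since no other level is given for H4.

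**The concern.** Mediation of an intervention effect needs two links: condition must shift the mediator, and the mediator must carry that shift to the outcome. The rule examines only the second, and only as an association between changes. Self-efficacy gains may precede symptom gains in every arm, the waiting list included. The rule would then indicate mediation even if expert-patient support did nothing to self-efficacy.

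The directional part has its own fault. A p value below 0.05 in one regression and above it in the other is not a test that the two paths differ. Two equal paths can fall on opposite sides of 0.05 by chance. A genuine mediator can also fail the rule because the inverse path is real as well.

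At stake is the trial's statement about how expert-patient support works. H4 is one of two named hypotheses under the second aim.

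**Working it through.** **1. Hypothesis against test.**
- Hypothesis: condition → T0–T1 self-efficacy change → long-term outcome.
- Forward model: T1–T5 outcome change on T0–T1 self-efficacy change.
- Inverse model: T1–T5 self-efficacy change on T0–T1 outcome change.
- Rule: forward p < 0.05 and inverse p ≥ 0.05.

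The link from condition to self-efficacy appears in neither model nor in the rule. No product of paths is estimated, and the two paths are not compared.

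**2. Arithmetic of the contrast.** The protocol gives no figure for H4 to reproduce. If the two tests were independent and each had power p, then P(forward significant, inverse not) = p(1 − p).
- p = 0.3: 0.3 × 0.7 = 0.21
- p = 0.5: 0.5 × 0.5 = 0.25
- p = 0.8: 0.8 × 0.2 = 0.16
- No relation in either direction: 0.05 × 0.95 = 0.0475 per outcome. Over two outcomes, if independent, 1 − (1 − 0.0475)² = 0.093.

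So with equal paths the rule still declares a one-way effect in 16% to 25% of trials over this range of power.

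**3. Simulation with a null intervention.**

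From the protocol: alpha 0.05 two-tailed; 88 per condition, so 88 × 4 = 352 randomised, 352 × 0.75 = 264 after the anticipated 25% dropout by T1, and 88 × 2 = 176 if only the two support arms were used. The 198 in the table (264 × 0.75) is an assumed smaller case. The protocol does not say which arms enter H4; Statistical analyses includes everyone randomised, with multiple imputation.

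Assumed, not in the documents: correlation of self-efficacy change and symptom change within a period -0.4; autoregression of each change on its own earlier change -0.3; standardised cross-lags as shown. The synchronous-change correction is read in one possible way, as adding the other variable's concurrent T1–T5 change, with residual correlation -0.4.

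Percentage of trials in which the rule indicates mediation, with no effect of condition on anything (2000 runs per setting):

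| N | One-way -0.20, own prior change only | Same, effect of condition on self-efficacy also required | One-way -0.20, concurrent change also adjusted | Equal paths -0.20, own prior change only | Equal paths -0.20, concurrent change also adjusted |
|---|---|---|---|---|---|
| 352 | 87 | 3 | 42 | 6 | 0 |
| 264 | 81 | 5 | 55 | 14 | 0 |
| 198 | 69 | 3 | 65 | 23 | 1 |

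Over one-way paths of -0.20 to -0.25 and N from 176 to 352, the range is roughly 63% to 96% with own-change adjustment. The top is the ceiling set by the inverse test's own 5% error rate, give or take simulation error. With concurrent change also adjusted it is about 33% to 61%. Separately programmed runs differ by several points, as the table's last row shows, so these are orders of size only. Equal-path rates run from 0% to 28% across the settings tried.

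In the equal-path case at N = 352 with own-change adjustment, the forward path is significant in 93% of trials, yet the rule fires in 6%. It therefore also discards a real forward path when the inverse path is real.

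**4. No cross-lag at all.** With own-change adjustment the rule fires in about 5%, as step 2 predicts. With concurrent change also adjusted it fires in about 20%. Let S1 and S2 be the early and late self-efficacy changes, and Y1 and Y2 the symptom changes:
- S2 = -0.3·S1 + e
- Y2 = -0.3·Y1 + f, where f = -0.4·e + u (equal residual variances)
- Substituting e = S2 + 0.3·S1 gives Y2 = -0.3·Y1 - 0.4·S2 - 0.12·S1 + u

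The adjusted regression thus shows a coefficient of -0.4 × 0.3 = -0.12 for early self-efficacy change where no cross-lag exists. This reading of the correction does not rescue the rule.

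**The case against.** **The steps of the hierarchical regressions are not listed.** A reader might infer that condition is excluded from every H4 model. The article does not support that: a condensed text may leave covariates to a fuller plan. What can be said is that no condition term is stated. This does not remove the point, because condition entered as a covariate would still leave its effect on self-efficacy unestimated, and the stated rule would not use it.

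**The analysis section can be read as asking about temporal precedence.** Its restatement of H4, with the reverse direction ruled out, fits a cross-lagged design. That stands for the regressions themselves. It does not justify calling the result mediation, nor answer H4 as worded under Aims and research questions.

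**A null effect would be visible elsewhere.** Intervention effectiveness analyses compares the conditions on EDE-Q over T0–T1, T1–T3 and T1–T5. This tempers any prediction of what would be published, but the H4 conclusion is not made conditional on those results.

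**The simulated rates are driven by their inputs.** This stands. The one-way runs build in a real cross-lag, so a high rate is largely power to detect it. Leaving out the synchronous-change correction raises most of these rates. No cross-lag or residual correlation is given in the documents.

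**Conclusion.** The point holds as a mismatch between a stated hypothesis and a stated decision rule. H4 concerns mediation of the intervention's effect; the rule can indicate mediation with no effect of condition on self-efficacy, and its significant-versus-not contrast does not establish direction. This follows from the text and needs no simulation.

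The size is illustrative and rests on the assumptions listed in the working. A reader might take 63% to 96% as the rule's false-positive rate. It is not: it is how often an assumed real association would be detected and then mislabelled. With no cross-lag and own-change adjustment, the rate is about 5% per outcome. The equal-path rates depend too much on the model to support a single figure.

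A reader might also infer that the trial's main result is at risk. It is not: H4 belongs to the second aim and the primary EDE-Q comparison is untouched. The change should be made before the H4 analysis is run.

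**What to change.** In Moderator and mediator analyses, define mediation for H4 as the indirect effect of randomised condition, expert-patient support versus no support:
- Path a: condition on T1 self-efficacy, adjusted for T0 self-efficacy.
- Path b: T1 self-efficacy on the T5 outcome, adjusted for condition, T0 self-efficacy, and the T0 and T1 outcome.
- Report a × b with a bootstrap 95% confidence interval for each outcome, and claim mediation only if the interval excludes 0.

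Keep the cross-lagged regressions as a sensitivity analysis. Report both paths with confidence intervals, drop the significant-versus-not rule, and describe the result as temporal precedence.

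The cost is revised wording and one more model. GSES, EDE-Q and social support at T0, T1 and T5 are already needed for the planned change scores, and condition is known. The downside is that a mediation claim becomes harder to reach. In the simulations, adding only a significant effect of condition on self-efficacy to the existing rule cut the null-intervention rate to between 0% and 4.6%. Path b is still not randomised, so the claim would still rest on the adjustment being adequate.

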### Statistical analyses

All statistical analyses will be conducted in SPSS version 25 and the R statistical programming environment [85]. A two-tailed significance level of *α* = .05 will be maintained throughout the analyses unless indicated otherwise. All analyses will be conducted according to the intention-to-treat (ITT) approach. This means that all participants who underwent randomization, even those who withdrew from the study or deviated from the protocol, are included in the analyses. For the effectiveness analyses, both ITT and completers analyses will be conducted. A participant is considered a completer when he/she has completed at least five monitoring assessments (i.e., Featback only condition), five support sessions (i.e., expert-patient support only condition), or both (i.e., Featback plus expert-patient support condition).

Missing data will be handled using multiple imputation [86]. Multiple imputations using predictive mean matching will be conducted in the statistical programming environment R [85]. Interactions will be taken into account in the imputation procedure [87]. Multiple imputation methods have several advantages over complete-case analyses or single imputation techniques and are therefore highly recommended [86, 88].

Homogeneity of groups (i.e., between-group differences) will be assessed at baseline (T0) using chi-square tests for categorical variables and ANOVAs for continuous variables. Additionally, homogeneity of variances will be assessed using Levene’s statistic, and non-parametric testing will be used when appropriate.

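### H4 tests mediation on two outcomes and accepts either one at an uncorrected 0.05, although H3 and H5 are Holm-corrected

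*Protocol article*

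**What the plan says.** All places are in the protocol article.

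- **Aims and research questions.** H3 and H4 are presented as hypotheses in addition to the exploratory work of the second aim. H4 states that changes in self-efficacy "mediate subsequent long-term effects of the intervention on ED-related symptoms and experienced social support".
- **Statistical analyses.** A two-tailed significance level of 0.05 "will be maintained throughout the analyses unless indicated otherwise".
- **Moderator and mediator analyses, H3.** Three outcomes at two time points are analysed, "resulting in six linear regression analyses that need to be conducted. We correct for multiple testing for these analyses using Holm" (Holm's method). This sentence closes the H3 text and comes before H4 begins.
- **Moderator and mediator analyses, H4.** Regressions are run "with post-intervention to long-term follow-up change of ED-related symptoms and experienced social support as dependent variables", with the T0–T1 change in self-efficacy as predictor. The inverse regressions are run as well. The decision rule is: "If the initial relationship is significant and the inverse relationship is not", then "a mediation effect of self-efficacy on ED-related symptoms and/or experienced social support is indicated". The only corrections named are these: "Corrections for autocorrelation and synchronous change will be applied to the mediation analysis".
- **Satisfaction and intervention usage analyses, H5.** Satisfaction and usage are tested with Holm's method.
- **Elsewhere.** The post hoc tests for H2 and the exploratory moderator search are Bonferroni-corrected.

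**The concern.** H4 is a named hypothesis with two chances of a positive finding, and the article writes out its decision rule in full. The adjustments for autocorrelation and synchronous change belong to the regression model and do nothing about the number of tests. By default, therefore, each forward test runs at 0.05 and a finding on either outcome counts.

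This does not fit the article's own practice. It treats several outcomes under one hypothesis as a family in H3 and again in H5, and it corrects even the moderator search that it calls exploratory. It gives no reason for handling H4 differently.

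At stake is the trial's test of how expert-patient support is thought to work. Under some conditions a false mechanism claim on at least one outcome is more likely than the stated 0.05 suggests. The primary comparison is not affected.

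**Working it through.** **Inputs from the document**
- Level per test: two-tailed 0.05 (Statistical analyses).
- Two forward tests, one per outcome (H4 text).
- One inverse test per outcome, which must be non-significant (H4 text).
- A claim is possible on either or both outcomes (H4 text).

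**Inputs assumed**
- The correlation between the two outcome tests is not given. The range 0 to 0.9 is shown.
- In the base case there is no cross-lagged effect in either direction, and the forward and inverse tests are independent of each other.

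The plan states no family error rate for H4, so the only figure of its own to start from is the 0.05 per test.

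**Step 1. One outcome.** A false claim needs a significant forward test and a non-significant inverse test: 0.05 × (1 − 0.05) = 0.0475, or 4.75%.

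**Step 2. At least one of two outcomes, independent tests.**
- Without the inverse condition: 1 − 0.95² = 0.0975.
- With it: 1 − (1 − 0.0475)² = 0.0927.

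**Step 3. Correlated tests.** Normal-theory simulation, 4 million draws per setting, same rule:

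| Correlation | Uncorrected, either direction | Uncorrected, hypothesised direction only | Smaller forward p-value held to 0.025 |
|---|---|---|---|
| 0 | 9.3% | 4.7% | 4.7% |
| 0.3 | 9.1% | 4.5% | 4.6% |
| 0.5 | 8.7% | 4.3% | 4.4% |
| 0.7 | 8.0% | 4.0% | 4.1% |
| 0.9 | 6.7% | 3.4% | 3.5% |

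Two raw-data simulations of the cross-lagged regressions, with 8,000 runs per setting and correlations of 0 to 0.7, agree. With 264 participants (assumed) and adjustment for the outcome's own earlier change, the uncorrected rate was 7.7% to 9.1%. With 200 participants (assumed) and adjustment for synchronous change as well, it was 8.0% to 9.5%.

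**Step 4. Direction.** If only effects in the hypothesised direction count, the nominal rate is 2.5% per outcome. At independence the family rate is 1 − (1 − 0.025 × 0.95)² = 0.0469.

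**Step 5. Real inverse effects.** If the inverse test has power *w*, the rate per outcome is 0.05 × (1 − *w*). For independent outcomes:
- *w* = 0.20: 1 − (1 − 0.04)² = 0.0784
- *w* = 0.50: 1 − (1 − 0.025)² = 0.0494
- *w* = 0.80: 1 − (1 − 0.01)² = 0.0199

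**Step 6. Holm over the two forward tests.** Holm rejects at least once only if the smaller p-value is at or below 0.025. At independence this gives 1 − 0.975² = 0.0494 before the inverse condition and 1 − (1 − 0.025 × 0.95)² = 0.0469 after it. Holm's second step matters only when the first outcome is blocked by its inverse test and the second has a p-value between 0.025 and 0.05. At independence that adds 2 × 0.025 × 0.05 × 0.025 × 0.95 = 0.00006, so the last column of the table stands to within rounding. The 200-participant simulation with Holm gave 4.9%, 4.9%, 4.3% and 3.7% at correlations 0, 0.3, 0.5 and 0.7.

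**The case against.** The strongest reply is that the either-or wording is distributive: the claim attaches to whichever outcome passes, and nothing says that one significant outcome confirms H4 as a whole. Read that way, each claim is made at about 4.75% and there is no single joint claim to inflate. This stands as a reading of each claim taken singly. It does not explain why the outcomes of H3 and H5, which could equally be read one by one, are corrected together.

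A reader might infer that H4 is simply tested at nearly twice its alpha. The document does not support that without conditions. The upper figures need no effect in either direction, both directions counted, and a correlation up to about 0.7. H4 is directional in substance, and false claims that favour the theory stay below 5%. If inverse effects are real, the uncorrected rule can also fall below 5%, though that protection comes from an unknown effect and not from the design.

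A reader might also infer that the hypothesis, which joins the two outcomes with *and*, contradicts the decision rule. That does not follow: the *and* can simply list two outcomes, and a finding on one would be reported as mediation on that named outcome.

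Nor is H4 the only uncorrected place. The H1 comparisons repeated for T1–T3 and T1–T5, and the *t* tests on costs and effects, carry no stated correction either. The inconsistency is with H3 and H5, the closest parallels. An analysis plan that is not shown might define an H4 family, but the article as written sets 0.05 by default.

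**Conclusion.** The point holds as a minor inconsistency. H4 is a stated hypothesis with two outcomes, each tested at an uncorrected 0.05, in a plan that applies Holm to the comparable sets of outcomes.

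Each single-outcome claim is controlled at about 4.75%. The chance of at least one false claim is about 8% to 9.3% for assumed correlations of 0 to 0.7 and about 6.7% at 0.9, provided that no cross-lagged effect exists in either direction and both directions count. It is about 4.0% to 4.7% for correlations 0 to 0.7 if only the hypothesised direction counts, against a nominal 2.5% per outcome. It is 4.9% if the inverse tests have 50% power and the outcomes are independent. The size therefore depends on quantities that the document does not give, while the missing correction is plain from the text.

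**What to change.** Add to the H4 text in Moderator and mediator analyses that:
- the two forward regressions (eating disorder symptoms and social support) are corrected with Holm's method, as for H3 and H5;
- the inverse regressions stay at an uncorrected 0.05;
- mediation is claimed only for the named outcome that passes.

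The second item needs stating because the inverse tests decide whether a claim is allowed, and a stricter level for them would make claims easier. Under the assumptions above, with correlations of 0 to 0.7, this holds the family rate at about 4% to 5%.

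The cost is one or two sentences and no new data. Power for a single-outcome claim falls slightly, because the smaller forward p-value must then reach 0.025. Requiring both outcomes to pass would also control the error, but it is not recommended: it rules out any single-outcome claim, costs more power when only one path is real, and is a debatable change to the hypothesis.

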#### Satisfaction and intervention usage analyses

(H5) To examine the fifth hypothesis that Featback with weekly expert-patient support results in an increased satisfaction and intervention usage, an ANOVA will be conducted to compare mean scores of satisfaction and intervention usage at T1 (i.e., directly after the intervention) between the three active intervention conditions. We correct for multiple testing for these analyses using Holm’s method.

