## Methods

### Design

Since the present study is a continuation of previous work of this research group, the methodology described here will be similar and in some parts identical to the previous design [19]. The current study describes an RCT with a two-by-two factorial design with repeated measures to create four different conditions: (1) Featback, comprising psychoeducation and a fully automated self-monitoring and feedback system, (2) Featback with weekly individualized support by an expert patient through e-mail or chat, (3) weekly individualized support by an expert patient through e-mail or chat, and (4) a waiting list. A description of the content of the interventions for each condition is presented below. After screening, all eligible participants are asked to give informed consent and fill in online baseline measures (T0). Subsequently, they will be randomized to one of the four conditions. An independent researcher will conduct randomized allocation by using the SPSS function to produce random numbers. Hence, the main researcher will be blind to the randomization process. Randomization will take place in blocks of 40 participants. The current design does not allow expert patients to be blinded to the study goal, since they are required to help participants with their ED or ED-related problems to the best of their abilities within the intervention protocol. Naturally, expert patients know that the individuals they have contact with via e-mail or chat are randomized to one of the expert-patient support conditions. Similarly, participants are not blinded concerning the condition allocation.

After 8 weeks (intervention period or waiting period), participants are invited to complete the post-intervention assessment (T1). Finally, a link to the online follow-up questionnaires will be sent to them 3 (T2), 6 (T3), 9 (T4), and 12 (T5) months after T1 (see Fig. 1). Ethical approval has been obtained by an independent medical ethics committee (CME LUMC Leiden, file number NL64553.058.18). The Standard Protocol Items: Recommendations for Interventional Trials (SPIRIT) checklist is provided as Additional file 1.

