### Interventions

#### Featback

All participants in the Featback conditions can access the Featback website on which comprehensive information on EDs and their causes and consequences can be found (i.e., psychoeducation). The psychoeducation will be purely self-guided, meaning that participants are free to choose what to read and when. For the monitoring and feedback system, participants receive an invitation by e-mail to complete a monitoring assessment weekly. This questionnaire consists of four 4-point Likert items assessing ED-related behaviors, namely (1) excessive concerns with body weight and shape, (2) unbalanced nutrition and dieting, (3) binge eating, and (4) compensatory behaviors. When participants have completed the questionnaire, a supportive feedback message will be automatically generated according to a pre-defined algorithm, which addresses their reported behaviors (healthy or unhealthy range) and patterns of change (improved, deteriorated, or unchanged) on each of the assessed ED-related behaviors. Hence, the automated messages vary in content depending on the problems that users report. The messages contain a summary of self-reported eating problems, psychoeducation, and guidance on how to counter ED-related symptoms, which are formulated in a supportive and reinforcing way. Table 1 illustrates one of these automatically generated messages.

**Table 1 Tab1:** Example of an automatically generated Featback message. *Note*: This message reflects the content when a participant indicates in the weekly monitoring that she or he worries about food, has at least one day in which she or he restricts food intake, and has had more binges and compensation behavior than in the previous week. The message is translated freely from the Dutch version

“We are concerned about your eating problems. You indicate that last week you have been worrying about food and your body, you have not eaten sufficiently every day and have had more days on which you dealt with binges and compensatory behaviors. That’s no small thing you’re dealing with :(.	

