##### User satisfaction

To assess the user satisfaction of Featback, a questionnaire was developed. Among other questions, participants are asked how they rate the quality of support they have received from Featback, whether Featback helped them to more effectively cope with their eating-related problems, and the extent to which they were satisfied with Featback in general. Additionally, participants are requested to rate the various components of Featback and address positive points as well as points for improvement (e.g., they are asked what they liked or disliked most and how the intervention can be developed further).

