##### Intervention usage

Intervention usage will be operationalized by the amount of weekly monitoring assessments a participant has completed during the intervention period (range 0–8). Additionally, to be able to further investigate the relation between intervention usage and the effectiveness of Featback, the number of received support sessions of participants (one for each received e-mail or chat session) will be recorded.

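### H5 is a two-arm claim, but it is tested by a three-arm ANOVA on a usage score counting forms that the support-only arm is not given

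*Protocol article*

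**What the plan says.** The protocol article states H5 under Aims and research questions as a comparison of two arms: "Featback with weekly expert-patient support will enhance intervention usage as well as satisfaction with the intervention compared to Featback alone".

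The section on satisfaction and intervention usage analyses tests it with an ANOVA to "compare mean scores of satisfaction and intervention usage at T1 (i.e., directly after the intervention) between the three active intervention conditions", with Holm's correction. The third arm is expert-patient support without Featback.

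The Intervention usage section fixes the score: "Intervention usage will be operationalized by the amount of weekly monitoring assessments a participant has completed during the intervention period", with range 0–8. It adds that "the number of received support sessions of participants (one for each received e-mail or chat session) will be recorded", for the purpose of studying how usage relates to effectiveness. Sessions are not part of the usage score.

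Monitoring is part of Featback. The Design section describes condition 1 as "Featback, comprising psychoeducation and a fully automated self-monitoring and feedback system" and lists only weekly support for condition 3. The monitoring invitation is described in the Featback subsection, which opens with "All participants in the Featback conditions can access the Featback website".

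The User satisfaction section begins "To assess the user satisfaction of Featback, a questionnaire was developed".

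**The concern.** The test and the hypothesis concern different sets of arms. H5 says nothing about support without Featback, yet that arm enters the F test. On usage it cannot score in the same way as the other two, because the thing counted is a Featback component.

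A significant omnibus result could therefore reflect only what each arm was offered. It could be reported as support for H5 when support made no difference to usage among Featback participants. H5 is the only numbered hypothesis under the third aim (practical experiences with Featback).

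**Working it through.** **Does the support-only arm receive monitoring forms?** Four places indicate that it does not.
- Design lists monitoring under Featback and only expert-patient support for condition 3.
- The Featback subsection describes monitoring for the Featback conditions.
- Under Statistical analyses, a completer needs five monitoring assessments (Featback only), five sessions (support only) or both (combination).
- Ethical considerations has severe problems in the support-only arm noticed through chats or e-mails.

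One sentence in Ethical considerations mentions a weekly monitoring questionnaire without limiting it to certain arms. Taken literally, it would also cover the waiting list, so the arm-specific text is the better guide.

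**What can the usage test mean?**
1. Support-only participants score 0, as the definition literally implies. The F test then picks up the absence of the component.
2. Usage is not applicable in that arm. A three-arm ANOVA cannot be computed as written.
3. Sessions stand in for forms. The arms are then compared on different quantities, contrary to the definition.

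**The plan's own figure.** The protocol states no power or error rate for H5. Its one calculated sample size, 264, does reproduce. With f = 0.15, two groups, two measurements and correlation 0.5, the noncentrality is 0.15² × 264 × 2 / (1 + 0.5) = 7.92. Power is 0.8007, and 264 is the smallest even total reaching 0.80.

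**Inputs for the H5 check.**
- n per arm: 88 as planned, or 88 × 0.75 = 66 after the anticipated 25% dropout.
- Two-sided alpha: 0.05.
- Assumed, because the protocol gives no values: mean usage 0.5 to 6 forms, and beta-binomial spread with within-person correlation 0.2 to 0.7.
- Both Featback arms drawn from the same distribution, so H5 is false for usage. Support-only set to 0. There were 4,000 replicates per setting.

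**Why reading 1 rejects.** With arm means m, m and 0, the between-arm sum of squares is n × (2/3)m², and the average within-arm variance is (2/3)SD². For n = 66, m = 4 and SD = 2.99:
- between: 66 × (2/3) × 16 = 704
- within: (2/3) × 2.99² = 5.96
- noncentrality: 704 / 5.96 ≈ 118

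The H5 contrast contributes nothing to this, since its two means are equal.

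**Simulated rejection of the three-arm ANOVA, equal usage in the two Featback arms**

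| Assumed mean forms | 88 per arm | 66 per arm |
|---|---|---|
| 0.5 | 92.6–100% | 67.9–100% |
| 1 | 100% | 99.9–100% |
| 2 to 6 | 100% | 100% |

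Ranges run over the assumed spreads (SD about 1.4 to 3.4 for means of 1 or more).

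**The same data, two Featback arms only.** Rejection was 4.2–5.6% over all settings, which is nominal.

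**Power of the two-arm contrast.** Borrowing d = 0.30 from the sample size section as an assumption, power = Φ(0.30 × √(n/2) − z). At alpha 0.05 this is 51% with 88 per arm and 41% with 66. At Holm's first step for two outcomes (alpha 0.025) it is 40% and 30%.

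**The case against.** The strongest reply is that the near-certain rejection depends on one coding choice. The protocol never says that support-only participants score 0, and its completer rule shows that the authors know adherence differs by arm. If usage is treated as not applicable, the arm drops out and the comparison becomes the two-arm one. This stands as a limit. A reader might infer that the test is significant by construction. It is not: the result needs the zero coding and an assumed mean, and it weakens when hardly any forms are completed. But the other readings do not rescue the stated test. One leaves it impossible to compute over three arms, and one mixes quantities.

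It can also be said that Holm's correction may refer to pairwise comparisons, one of which would be the right contrast, and that follow-up contrasts are commonly left to an analysis plan. The Holm sentence is ambiguous. Still, the section names no pairwise test, whereas the effectiveness section does specify post hoc tests for H2.

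Two further inferences go beyond the document:
- **Satisfaction.** A reader might conclude that the three-arm satisfaction comparison is equally invalid. The questionnaire is described as concerning Featback, but the Background counts coach contact as part of the Featback programme, one item rates the quality of support received, and the questionnaire is only summarised. Whether its items suit support-only participants is open.
- **Imputation.** A reader might conclude that multiple imputation will invent monitoring counts. The protocol imputes missing data but does not say that not-applicable values count as missing, so the risk is conditional.

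Finally, a count of completed forms does not need a T1 response, so 66 per arm may be too low for usage. Both sizes give the same conclusion.

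**Conclusion.** The point holds in this form: the stated omnibus test does not answer H5, and the usage score has no workable meaning in one of the three arms compared. With that arm coded 0, rejection under equal Featback usage is 99.9–100% for assumed means of 1 to 6 forms, against about 5% for the contrast that H5 states. Those figures rest on assumed usage means and spreads and on the inference, from several sections, that the support-only arm receives no monitoring.

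No error rate is shown for satisfaction. There the fault is only that the three-arm test is not the H5 contrast. This should be corrected, but it concerns a secondary hypothesis. The EDE-Q analysis and the sample size are not affected.

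**What to change.** In the section on satisfaction and intervention usage analyses:
- Make the H5 test for usage the contrast of Featback plus support versus Featback alone, on monitoring forms completed (0–8).
- Use the same contrast as the H5 test for satisfaction, and state that Holm applies over these two outcomes.
- Compare session counts separately, between the two support arms.
- State that monitoring counts are not imputed for the support-only arm.
- If wanted, keep a three-arm satisfaction comparison as descriptive, provided that the items apply to support-only participants.

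The cost is wording only. Form counts and session counts are already to be recorded. The authors should expect modest power for the two-arm contrast if the true effect is as small as d = 0.30, as the working shows.
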